#### Improved SALSA score

The SALSA scale [15] score decreases at least with 1 category in standardized categories of SALSA values as described in SALSA Scale Users Manual (Salsa Scale Users Manual, Version 1.1, July 2010)

#### Improved participation scale score

The Participation scale [16] score decreases at least 1 grade on the “Grades of participation restriction” scale (as described on P-scale form).

### Outcome criteria subclinical trial

#### Clinical motor impairment (MI)

Motor neuropathy resulting in weakness of the muscles innervated by a given nerve. A patient is diagnosed as having clinical motor impairment if the VMT score for a muscle test is 4 or less on the 0–5 (modified) MRC scale. If a score of 4 is found, the test will be repeated by a second assessor.

#### Clinical sensory impairment (SI)

A patient is diagnosed as having sensory impairment of a nerve if the monofilament threshold is increased by three or more monofilament levels on any site, two levels on one site AND at least one level on another site, OR one level on three or more sites for one nerve.

#### Subclinical nerve function score (SNFS)

The SubClinical Nerve Function Score (SNFS) will be computed for NC parameters (amplitude and latency) and warm detection threshold, where non-impaired parameter adds 1 point to the overall score.

#### Improved SNFS

SubClinical Nerve Function Score increased with at least 1 point

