### Entry criteria Subclinical trial

Any one parameter (Motor Nerve Conduction, Sensory Nerve Conduction, Warm Detection Threshold) abnormal in at least two nerves or any two parameters abnormal in at least one nerve. VMT and MFT values are normal.

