#### Deteriorated SNFS

SubClinical Nerve Function Score decreased with at least 1 point

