#### Subclinical nerve function tests

When new patients show no abnormal values by VMT and MFT they will be tested further for possible inclusion in the Subclinical trial. For detecting subclinical neuropathy sensory and motor Nerve Conduction Studies (NCS), carried out with the Neurocare 2000® EMG machine (BioTech Ltd, Mumbai), and Warm Detection Threshold (WDT) test, using the TSA II (MEDOC, Israel), will be performed. NCS and WDT will take place in an air-conditioned room at approximately 20-25°C.

All assessments will be carried out at both sides of the body. Table 1 shows which nerves will be tested and methods used. MFT and VMT will be assessed at start of the trial and subsequently every month in both studies and follow-up periods on all subjects. WDT, Sensory Nerve Conduction (SNC) and Motor Nerve Conduction (MNC) will be carried out at baseline, end of treatment period (20 weeks) and at 12 and 18 months. For the Clinical trial additional information will be obtained using the Reaction Severity Scale (RSS) [25], the Screening of Activity Limitation and Safety Awareness (SALSA) scale [26] and the Participation Scale [27]. All scales will be filled in at baseline, end of treatment period (32 weeks), 12 and 18 months.

**Table 1 T1:** Nerves assessed by the different methods

**Nerve**	**VMT**	**MFT**	**MNC**	**SNC**	**WDT**
Trigeminal		blink			
Facial	x				
Ulnar	x	x	x	x	x
Median	x	x	x	x	x
Radial	x	x		x	x
Common peroneal	x		x		
Post. Tibial	x	x	x		x
Sural		x		x	x

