#### Normative studies

To determine normative values for WDT and NCS for each centre, outliers are excluded before limits of normal function are calculated using an approach based on regression analysis taking into account age-related trends. The 97.5^th^ percentile is used to define abnormal function.

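### A 1-point change on an SNFS of about 42 yes/no parameters makes no allowance for measurement error, so a large share of stable patients would be classed as improved or deteriorated

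*Protocol article*

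**What the plan says.** All references are to the protocol article.

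- **Scoring, under Subclinical nerve function score (SNFS):** the items are the two conduction measures of each nerve, namely amplitude and latency, together with the WDT. Each is judged yes or no, "where non-impaired parameter adds 1 point to the overall score".
- **Upward category, in its own short definition:** a patient is placed here when the "SubClinical Nerve Function Score increased with at least 1 point".
- **Downward category, defined as the mirror image:** a patient is placed here when the "SubClinical Nerve Function Score decreased with at least 1 point". Unchanged is therefore an exactly equal score.
- **Subclinical nerve function tests:** the nerves and the methods used for each are listed in Table 1, and on laterality the text says "All assessments will be carried out at both sides of the body". The tests are done at baseline, 20 weeks, 12 months and 18 months.
- **Normative studies:** limits are set per centre, and the 97.5th "percentile is used to define abnormal function".
- **Entry criteria Subclinical trial:** one parameter "abnormal in at least two nerves or any two parameters abnormal in at least one nerve", with normal VMT and MFT.
- **Reliability and normative studies; Reliability studies:** inter-tester reliability was examined for every test, but no result is given.
- **Outcome measures, The Subclinical trial:** clinical NFI is primary. Secondary outcomes concern WDT, SNC and MNC.
- **Secondary outcomes:** analysis of (co)variance is named for continuous measures.

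**The concern.** The score adds up many dichotomised readings, and the responder rule reacts to a net change of one of them. Each reading carries measurement error, and those near the limit can cross it in either direction with no change in the nerve. With dozens of readings per patient, at least one crossing is likely even when each is rarely wrong. Patients also enter because some readings were abnormal, so on retest some of those readings will return to normal by chance.

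Other outcome definitions in the article leave a margin. The Reaction Severity Scale needs 3 points on the sum or 2 on one item. A monofilament change needs a three-level rise on one site or a defined combination across sites. A VMT score of 4 is checked by a second assessor. The SNFS rule has no comparable margin.

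At stake is whether the improved and deteriorated proportions say anything about subclinical nerve function, and whether a real treatment effect on it could be seen through them.

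**Working it through.** **1. Length of the score.** From Table 1, per side: MNC 4 nerves (ulnar, median, common peroneal, posterior tibial), SNC 4 (ulnar, median, radial, sural), WDT 5 (ulnar, median, radial, posterior tibial, sural). With two sides, and amplitude and latency for each conduction test:

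- MNC 4 × 2 × 2 = 16
- SNC 4 × 2 × 2 = 16
- WDT 5 × 2 = 10
- Total 42

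If each conduction test counts once: 8 + 8 + 10 = 26. The article does not state the maximum. One point in 42 is 2.4% of the scale. With limits at the 97.5th percentile, a healthy person averages 42 × 0.025 = 1.05 abnormal parameters.

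**2. How many flips are enough.** Take a patient with k abnormal parameters and no true change. Let each parameter flip independently with probability f between visits. Then U ~ Bin(k, f) parameters turn normal, D ~ Bin(42 − k, f) turn abnormal, and P(classed as changed) = 1 − P(U = D).

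Example with k = 2, f = 0.02:
- no flips: 0.98^42 = 0.428
- one flip each way: (2 × 0.02 × 0.98) × (40 × 0.02 × 0.98^39) = 0.0392 × 0.364 = 0.014
- P(changed) = 1 − 0.442 = 0.558

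| Flip rate f | Classed as changed, k = 2 to 8 |
|---|---|
| 1% | 33–34% |
| 2% | 52–56% |
| 3% | 65–70% |
| 5% | 78–86% |

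One half is reached at f = 1.7–1.9% for 42 items and 2.8–3.2% for 26 items.

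**3. Readings near the cut-off.** Reliability is an assumption, because the article gives no figure. Each of 42 independent parameters has true variance r and error variance 1 − r, a cut-off at 1.96, and a mean shift of 0, 0.5 or 1 SD towards abnormal. Patients with at least 2 abnormal parameters are kept and retested with fresh error and no true change. Over r = 0.7 to 0.95, 57–84% are classed as changed and 37–67% as improved. Improved exceeds deteriorated because of selection at entry. The excess is largest with no shift (67% v 11% at r = 0.7) and nearly vanishes at a 1 SD shift (42% v 42%), where almost everyone qualifies.

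A second simulation used the Table 1 layout, the article's entry rule and correlated parameters. It gave 52–93% changed over r = 0.98 to 0.6. At r = 0.9 it gave 71–87% changed: 45–57% improved and 18–34% deteriorated.

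**4. Readings far beyond the cut-off.** Let abnormal parameters revert with probability only 0.02, and let normal parameters turn abnormal at the rate implied by r under a bivariate normal (1.44% at r = 0.8, 1.04% at 0.9, 0.75% at 0.95). By the formula in step 2 with k = 2 to 6, 44–45% are classed as changed at r = 0.8, about 36% at 0.9 and 28–30% at 0.95. Here the false changes are mostly deteriorations (for example 43% v 2% at r = 0.8, k = 2).

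**5. Dilution.** If true responders are always called improved, and the rest are called improved by chance with probability q in both arms, a true difference Δ is observed as (1 − q)Δ. With Δ = 20 points as an illustration and q = 0.45 to 0.57, this is 20 × 0.55 = 11 to 20 × 0.43 = 8.6 points.

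**The case against.** The strongest reply is that the size depends on an unreported figure. A reader might infer that most stable patients will be misclassified. The article does not support that as a fact: if fewer than about 1.7% of parameters flip, or the abnormal nerves are well beyond the limit, the share is a minority. This stands, and the size has to be given as a range. Independence between parameters of one nerve is also a simplification, although the version with correlated parameters still shows heavy misclassification.

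A reader might also infer that a high improved rate could pass for benefit from prednisolone. Regression to the mean and retest noise act alike in both blinded, randomised arms, and no within-arm claim is planned. The harm is loss of sensitivity, not a spurious treatment effect. Nor does the article call the SNFS the main secondary outcome: it neither ranks the secondary outcomes nor names the SNFS among them.

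It can further be said that analysis of covariance is already available for continuous outcomes and that an unseen analysis plan may apply it to the SNFS. That is possible. But the article itself defines SNFS change only as two 1-point categories, so the rule as published is not cured by that general sentence.

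**Conclusion.** The point holds as a weakness in a secondary outcome definition. The 1-point rule on about 42 dichotomised parameters carries no margin for measurement error.

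The share of truly unchanged patients classed as changed is about 57–84% if reliability is 0.7 to 0.95 and many readings sit near the cut-off. It is about 28–45% if the abnormal readings are far beyond it (reliability 0.95 to 0.8). The share is large in either case, and a majority once about 2% of parameters flip (about 3% for 26 items). The excess of improved over deteriorated applies when readings cluster near the limit. It does not hold when the abnormal readings are extreme.

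The consequences are a diluted between-arm difference and within-arm proportions that cannot be interpreted. The primary outcome, clinical NFI by MFT and VMT, and its sample size are unaffected.

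**What to change.** Make the SNFS analysis a between-arm comparison of the score as a continuous measure at 20 weeks, 12 months and 18 months, by the analysis of covariance the article already names, adjusted for baseline SNFS and centre. State the maximum score and whether amplitude and latency each count.

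If improved and deteriorated categories are kept, report them as supportive only and set the threshold above the measurement error of the total score. The completed reliability studies can inform this only if they allow an estimate for the total. They are described as inter-tester and per test, not as repeats of the full panel over months, so any threshold from them may be a lower bound.

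The continuous analysis costs only wording and needs no new visits or patients. The downside is that fewer patients would be labelled improved or deteriorated, and a mean difference in score is less simple to state than a proportion.

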#### Deteriorated SNFS

SubClinical Nerve Function Score decreased with at least 1 point

### Design of study

The TENLEP study consists of two multi-centre randomized triple blind controlled trials, both with two treatment arms, to study the effectiveness of prednisolone treatment restoring (Clinical trial) and in preventing (Subclinical trial) clinical nerve function loss.

Six institutions in four different countries participate in this study: Nepal (Lalgadh Hospital and Anandaban Hospital); India (JALMA Institute for Leprosy -Agra and Foundation for Medical Research-Mumbai); Bangladesh (Nilphamari Hospital); and Indonesia ([name] Surabaya). Anandaban Hospital and [name] will only take part in the Clinical trial. All collaborative institutions are referral hospitals specialized in the detection and treatment of leprosy. At each institution a Principal Investigator (PI) is responsible for the research at that centre. The overall responsibility lies with the International Coordinator (dr. [name]), guided by an International Steering Committee.

#### Participants

In the Clinical trial leprosy patients with clinical NFI will be randomly allocated to either treatment of standard duration (20 weeks) or an interventional treatment of longer duration (32 weeks). Both multibacillary (MB) and paucibacillary (PB) patients diagnosed with clinical sensory and/or motor nerve impairment of less than six months duration are enrolled. For the Subclinical trial leprosy patients with subclinical neuropathy will be randomly divided into an intervention group and a placebo group. Newly registered MB and PB patients without clinical NFI but having subclinical sensory and/or motor neuropathy at diagnosis, or developing this within their first three months of MDT treatment, will be eligible for inclusion in the trial. Patients from the Subclinical trial developing NFI in the first three months of the trial can enter the Clinical trial, but only data of patients that were allocated to the placebo group of the Subclinical trial will be analyzed.

#### Inclusion and exclusion criteria

Patients included in the trials should be between 15 and 60 years of age, must give informed consent and should be free from conditions that may affect the peripheral nervous system, such as diabetes mellitus, and other active underlying diseases for example hypertension, osteoporosis and tuberculosis. Included patients receive deworming treatment with Mebendazol before steroid treatment starts. In both studies patients will be followed-up for 18 months. Excluded will be women pregnant at diagnosis, patients who need steroids for reasons other than recent NFI and patients with a single skin lesion on the trunk as the only sign of leprosy.

#### Randomization and blinding

In both trials patients will be randomly allocated to one of the two study arms. Randomization tables are provided by the statistician and drugs are labeled accordingly by the manufacturer. The key is held by the International Coordinator, Study Manager and PI of each centre and will be broken after the data analysis is completed or earlier for patients with adverse events, and new or worsening NFI.

#### Sample size calculation

For the Clinical trial a recovery of 60% is presumed for the standard regimen in the control group [17]. To detect a recovery of 70% in the treatment group, compensating for 20% of loss to follow-up, a total of 720 subjects need to be enrolled.

The INFIR study shows that of the leprosy patients having subclinical neuropathy 16% will eventually develop clinical NFI [1]. For the Subclinical trial we assume a reduction in patients developing clinical NFI by half in the treated group (8%). Anticipating a loss to follow-up of 20% at 18 months, a sample size of 275 subjects per trial arm is required. For both sample size calculations a one-tailed alternative hypothesis, 80% power and 5% significance is used.

#### Follow-up

Patients will be followed-up for 18 months. Nerve function is monitored by monthly VMT and MFT in both trials and assessments with NCS and WDT takes place at 20 weeks, 12 and 18 months from intake in the Subclinical trial. Participants can be withdrawn from the trials because of medical or clinical reasons or pregnancy. Subjects missing their appointment will be visited at home by research staff within two weeks when contact by cell phone is not possible or did not result in late attendance at the clinic. In cases when only one appointment is missed and medication is not taken for a maximum of one month, treatment will continue from the first package missed. The TENLEP trials started in April 2012, with a duration of intake of 1.5 years.

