To examine treatment of clinical NFI several studies have been conducted using prednisolone. In one cohort the WHO recommended prednisolone regimen (starting with 40 mg prednisolone/day, tapered down over 12 weeks [2]) was found not to be successful in the prevention and reversal of NFI in multibacillary (MB) patients treated for reactions or neuropathy [10]. Also a 16-week prednisolone regimen, usual practice nowadays, was found not to be very effective in two randomized controlled trials (RCT) [11,12]. One trial was in patients with Type 1 Reactions and/or NFI, receiving either prednisolone or prednisolone with intravenous methylprednisolone. Close to 50% of the patients required additional prednisolone during or after the treatment period [11]. The second RCT in MB patients with mild sensory impairment did not show a difference in NFI as measured with MFT 12 months after start of prednisolone treatment [12]. Van Veen et al. [3], reviewing RCTs comparing placebo to prednisolone treatment, conclude that studies so far have not provided enough evidence to draw robust conclusions about the long-term effect of corticosteroids on reactions and NFI. However, there is reason to assume that longer steroid treatment might be more beneficial, since one study showed that a 5 month corticosteroid regimen was significantly more effective than a 3 month regimen [13]. In TENLEP we aim to assess whether prednisolone treatment of 32 weeks duration is more effective than treatment of 20 weeks duration in restoring nerve function in patients with clinical sensory and/or motor NFI of recent onset (<6 mo), as detected by VMT and/or MFT.

The effect of prednisolone treatment on patients with subclinical neuropathy to prevent clinical NFI as determined with MFT and/or VMT has not been studied in a RCT before. The objective of the Subclinical trial is therefore to determine whether prednisolone treatment of early subclinical neuropathy, as detected with WDT and NCS, would prevent clinical sensory and/or motor function loss in leprosy patients. This paper presents the protocols for both the Clinical and the Subclinical trial.

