#### Improved nerve function

At least one nerve shows better results on Monofilament Test and/or Voluntary Muscle Test. The MF thresholds should be *reduced* by three or more monofilament levels on any site, two levels on one site AND at least one level on another site, OR one level on three or more sites for one nerve. VMT score should be *increased* by at least 1 point.

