#### Adverse events

Prednisolone has known adverse events, ranging from mild adverse events, such as moon face, fungal infections and acne, to serious adverse events such as peptic ulcer, osteoporosis glaucoma, cataract, psychosis, diabetes and hypertension [18,19]. Serious adverse events have not been encountered frequently in previous trials studying prednisolone for treating NFI in leprosy patients [20], however strict monitoring of adverse events will take place in the TENLEP trials. In case of serious adverse effects the PI will break the key and initiate an individualized treatment scheme. In the event of minor side effects additional medication will be prescribed according to normal protocol in the clinic, but the key will not be broken.

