### Outcome measures

#### The Clinical trial

The primary study outcome is the proportion of patients with restored and improved nerve function (of all nerves) measured by VMT/MFT at 18 months. Secondary outcomes are based on results of the Reaction Severity Scale, SALSA and Participation Scale (Figure 2). Furthermore, a Count of Nerve Function Impairment (CNFI) will be computed to measure the results of treatment on nerve function, with special interest for most commonly affected nerves. The CNFI will consist of the count of nerve function impairments detected by monofilament and VMT testing and will be validated in this trial.

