#### The Subclinical trial

The proportion of patients developing clinical NFI as measured by MFT and VMT is the primary outcome indicator (Figure 2). Secondary outcome measures focus on results of the specific assessments for detection of subclinical neuropathy (WDT, SNC and MNC).

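### Clinical trial: withdrawal from the trial itself for undefined clinical reasons, with the arm known to the centre, can leave the 18-month primary outcome missing because the patient did badly

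*Protocol article*

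**What the plan says.** All references are to the protocol article.

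- **Follow-up:** patients are followed for 18 months with monthly VMT and MFT, and missed appointments lead to a phone call or home visit. The same section says "Participants can be withdrawn from the trials because of medical or clinical reasons or pregnancy". What is left is the trial, not only the study drug, and no criteria are given.
- **Randomization and blinding:** the key is held by the International Coordinator, the Study Manager and the PI of each centre, and it "will be broken after the data analysis is completed or earlier for patients with adverse events, and new or worsening NFI".
- **Adverse events:** "In case of serious adverse effects the PI will break the key and initiate an individualized treatment scheme".
- **Outcome measures, The Clinical trial:** this section fixes the endpoint as follows: "The primary study outcome is the proportion of patients with restored and improved nerve function (of all nerves) measured by VMT/MFT at 18 months". Improvement is met when "At least one nerve shows better results on Monofilament Test and/or Voluntary Muscle Test", by stated margins. Neither definition mentions clinical withdrawal or prednisolone given outside the study regimen.
- **Background:** on an earlier 16-week trial, "Close to 50% of the patients required additional prednisolone during or after the treatment period".
- **Outcome measures, The Subclinical trial:** here the endpoint reads: "The proportion of patients developing clinical NFI as measured by MFT and VMT is the primary outcome indicator".

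**The concern.** Worsening NFI is a plausible clinical reason for taking a patient out, and it is also close to the opposite of the primary outcome. If withdrawal ends assessment, the 18-month value is missing because of what it would have shown. The rule on breaking the key adds a second problem: the person deciding on withdrawal may know the arm at that moment. A PI who learns that a worsening patient was on 20 weeks may act differently from one who learns that the patient was on 32 weeks. Missingness would then depend on both outcome and arm, and an analysis of patients with an 18-month value would no longer compare the groups as randomised. Assessments that were never made cannot be recovered by later statistical methods, so the wording matters during conduct.

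A related question is non-study prednisolone. It is more of the exposure whose duration is being compared, and the article itself reports that it was common in an earlier trial.

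**Working it through.** **Inputs from the article (Sample size calculation).** 60% control, 70% treatment, one-sided 5%, 80% power, 20% loss to follow-up, 720 in total. Equal allocation is assumed, since the ratio is not stated.

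**Reproducing 720.** The two-proportion formula with continuity correction gives 300 per arm; 300 × 1.2 = 360 per arm, or 720. Without the correction it gives 281 per arm; 281 / 0.8 ≈ 352 per arm, or 704, within 3% of 720. The stated figure stands.

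**Reference power.** Evaluable per arm: 720 × 0.8 / 2 = 288. Power = Φ[(difference − 1.645 × SE₀) / SE₁], where SE₀ uses the pooled rate and SE₁ the separate rates. With 60% v 70%, SE₀ = 0.0397 and SE₁ = 0.0395, so power = Φ[(0.10 − 1.645 × 0.0397) / 0.0395] = 81%.

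**If withdrawn failures were left out.** Let w be the share of an arm's patients who fail, are withdrawn and have no 18-month value. The observed rate becomes p / (1 − w) on 288 × (1 − w) patients. The article gives no value for w, so these are assumptions.

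| w, 20-week arm | w, 32-week arm | Evaluable | Observed rates | Difference | Power |
|---|---|---|---|---|---|
| 0 | 0 | 288 v 288 | 60.0% v 70.0% | 10.0 points | 81% |
| 15% | 10% | 245 v 259 | 70.6% v 77.8% | 7.2 points | 58% |
| 20% | 10% | 230 v 259 | 75.0% v 77.8% | 2.8 points | 18% |
| 10% | 10% | 259 v 259 | 66.7% v 77.8% | 11.1 points | 88% |

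Second row: 0.60 / 0.85 = 0.706 and 0.70 / 0.90 = 0.778. The last row matters as much as the others: with equal shares of patients withdrawn, the observed difference grows. The direction therefore depends on how withdrawals divide between arms.

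**If non-study prednisolone turned failures into 18-month successes.** Observed rate = p + (1 − p) × r × s, where r is the share of failures given it and s the share of those who then qualify. With r = 0.5 and s = 0.4, rates are 68% v 76% and power 69%; with s = 0.6, 72% v 79% and 62%. Both r and s are assumptions. The near-50% in the Background is a share of all patients in a different trial and does not supply r.

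**The case against.** A reader might infer that failures are dropped from the comparison or return as successes. The documents do not support that. The withdrawal sentence is permissive, and it sits in a section that promises 18 months of follow-up. Nothing says that assessment stops, that withdrawn patients leave the analysis, or that re-treated patients count as improved. They could equally be counted as failures. Analysis sets and missing-data rules commonly stand in the full protocol or SAP, neither of which is shown, so their absence from the article is no finding. All of this stands.

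The supporting figures are also weaker than they look:

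- The individualised scheme follows serious adverse effects, not relapse of NFI.
- The near-50% need for extra prednisolone comes from a 16-week trial in patients with Type 1 Reactions and/or NFI, some also given intravenous methylprednisolone.
- The presumed 60% may already include re-treated patients.
- The 288 per arm is already net of 20% loss, and the article does not say whether clinical withdrawals fall within that allowance, so the withdrawal scenarios may count some losses twice.

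Finally, 18-month status regardless of later treatment is a legitimate outcome for comparing two durations. Making non-study prednisolone a failure in the primary analysis would turn a decision by a possibly unblinded PI into part of the endpoint. That argues for a sensitivity analysis, not a change of primary outcome.

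What the objection does not remove is the wording itself. The article provides for withdrawal from the trial, leaves the reasons undefined, and lets the arm be revealed on worsening.

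**Conclusion.** The point holds for the Clinical trial, in a limited form. As written, the withdrawal rule permits an 18-month primary outcome to be missing because of failure, after a decision that may be taken with the arm known. Whether this happens, how often and in which direction cannot be determined from the documents. The fall in power to about 58% illustrates assumed withdrawal of 15% v 10%, with those patients left out of the analysis; it is not an estimate.

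Two wider readings should be set aside. The problem does not carry over in the same way to the Subclinical trial, where clinical NFI is itself the counted event and is looked for monthly, so a patient withdrawn for confirmed NFI has already had the outcome. Nor does it show 720 to be wrong, since that figure is reproduced from the article's own inputs.

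**What to change.** 1. In Follow-up, reword the rule as withdrawal from study medication. State that VMT and MFT continue to 18 months for every randomised patient who has not withdrawn consent.
2. Keep all randomised patients, in the arm assigned, in the primary comparison of 18-month status, whatever non-study prednisolone they received.
3. Record all non-study prednisolone. Beside the primary result, report a sensitivity analysis that counts patients given it for new or worsening NFI as not restored or improved.

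The cost is a little more tracing, one data field and one further analysis; monthly visits and home tracing are already in place. The sensitivity version needs cautious reading because it depends on treatment decisions that may be unblinded. Nothing here proposes when prednisolone should be given or study treatment stopped.
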